### Conclusion

HIV puts early neurodevelopment of HIV-infected and HEU children at risk [4, 11]. ECD interventions should form part of the management of HIV-infected and HEU children [25]. We will compare neurodevelopmental outcomes of early-treated HIV-infected children receiving an age-appropriate stimulation program with early-treated HIV-infected and HEU children not receiving an intervention.

## Limitations

Although comprehensive, the household survey may not include all confounding variables as development is influenced by innumerable factors. Children in the HEU control group would be exposed to the same confounders as the HIV-infected infants. Use of toys and materials is caregiver dependent—children may not be given the intervention in the home environment. Use of the intervention depends on parental acceptance in accordance with cultural norms and child rearing practices. Use of the intervention will be carefully explained to the caregiver and the caregiver will be encouraged to initiate play and interact with her infant. Sufficient time will be allowed for answering questions and repeating explanations. Study attrition will reduce the planned cohort size. Caregivers returning at incorrect study time points will result in children missing the ideal BSID assessment age. The following measures will be undertaken to maintain the cohort in follow-up. Caregivers will be provided with appointment cards for follow-up visits, and study visits will be scheduled for a mutually convenient day. Caregivers will receive a telephone call to remind them of their study visit the day before the visit is due. Visits will be rescheduled if caregivers are unable to honour their appointments. Completion of the assessment depends on the availability of trained assessors. Two assessors have been trained to ensure an assessor is available when scheduling appointments. Assessment bias may occur as assessors have not been blinded to the intervention group; however, assessors have been trained to conduct the assessment in a standardised manner for all participants.

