## Main text

The study is designed as a non-randomised controlled intervention study.

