### Study measures

Demographic and health-related variables will be collected from the patient’s files for participants enrolled in the existing cohort. Infant data includes birth history; serial anthropometric data; morbidity data; ART history; concurrent medication; immunisations; feeding history; and laboratory data i.e. HIV viral load, HIV total nucleic acid test, CD4 count, and full blood count (FBC). Maternal data consists of: serial anthropometric measurements; ART history; and laboratory data i.e. HIV viral load, CD4 count, and FBC. Permission for data use has been granted by the database holder and site clinical staff are aware of the aims and logistics of the study.

Composite scores for the three developmental subscales of the BSID-III which are administered with direct child interaction—cognitive, motor, and language—will be recorded [14]. Raw scores are converted to scaled scores which are used to derive the composite score for each subscale.

The household survey and the Parenting Stress Index-Short Form (PSI-SF) will be completed with the child’s caregiver. The household survey is a self-styled questionnaire gathering data about the household in which the child lives. Questions cover the following categories: family structure; number of household members diagnosed with HIV; parental nationality; employment; cigarette and alcohol use; water and sanitation measures; type of housing; exposure to sexual abuse and physical violence; childcare arrangements; and access to electricity and basic electronic household items. The household survey consists of a broad set of variables as ECD is influenced both negatively and positively by a myriad of factors [17–19]. The PSI-SF is the condensed version of a self-reported screening tool used to explore parental stress levels associated with parenting children aged 1 month–12 years [20]. Maternal HIV infection can impact parenting skills which in turn influences the child’s wellbeing, ECD and childhood outcomes [21, 22].

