### Data analysis

De-identified data from paper case report forms will be entered into a secure database. Statistical calculations will be performed using SAS version 9.4 (Cary, North Carolina, USA). Anthropometric Z-scores will be calculated using WHO software [23]. P-values will be two-tailed and p-values < 0.05 will be considered statistically significant.

Descriptive statistics will describe the characteristics of the early-treated perinatally HIV-infected children enrolled in the existing cohort in terms of demographics, growth parameters, and HIV-related factors. Composite cognitive, language and motor scores will be described. Continuous variables with normal distribution will be described using means and standard deviation with a 95% confidence interval. Frequency tabulations and percentages will be used to describe categorical variables. “At risk” of developmental delay will be defined as any composite score less than 85, and “delayed” as a score less than 70 [24]. Number of children in these two categories will be explored and associations between patient and disease characteristics investigated using the Chi squared test at 5% level of significance. Mean composite scores will be compared between children assessed at 12, 24 or 36 months of age using ANOVA.

Mean composite scores and number of children “at risk” or “delayed” in each subscale will be compared between early-treated HIV-infected and HEU infants assessed at 12 months of age. T tests will compare demographic, clinical and anthropometrical data between groups. The analysis will be expanded to include the HIV-infected infants having received the ECD intervention. The Chi squared test and Kruskall-Wallis 1-way ANOVA will be used to measure variable difference between groups.

Univariate and multiple regression analyses will be performed to establish associations with poor outcomes on the three subscales i.e. composite scores less than 70 or 85. Variables used to establish associations with poor outcomes will include maternal antenatal and postnatal health-related factors, infant birth data, infant health and HIV-related variables, and data pertaining to socioeconomic status and parental stress. Logistic regression will be conducted on various risk factors for each subscale and a score of ≤ 85 will constitute a poor outcome.

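### The Limitations section treats confounders as common to HEU and HIV-infected children, and the plan states no covariate-adjusted difference in composite scores for the HEU contrasts

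*Protocol article*

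**What the plan says.** The design is stated plainly under Main text: "The study is designed as a non-randomised controlled intervention study". On confounding, the Limitations section first concedes that "the household survey may not include all confounding variables as development is influenced by innumerable factors". It then reassures the reader that "Children in the HEU control group would be exposed to the same confounders as the HIV-infected infants".

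Under Data analysis, mean composite scores and the numbers at risk or delayed "in each subscale will be compared between early-treated HIV-infected and HEU infants assessed at 12 months of age". No covariate is named for this comparison. The next sentence plans t tests of demographic, clinical and anthropometric data between groups. The analysis is then widened to include the HIV-infected infants who received the programme: "The Chi squared test and Kruskall-Wallis 1-way ANOVA will be used to measure variable difference between groups".

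The same section plans univariate and multiple regression for poor outcome on each subscale. The candidate variables are maternal health, birth data, infant health and HIV-related factors, socioeconomic status and parental stress. Under Study measures, "Maternal data consists of: serial anthropometric measurements; ART history; and laboratory data i.e. HIV viral load, CD4 count, and FBC". The household survey covers employment, housing, smoking and alcohol, among other items.

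The primary aim (Introduction, repeated in the Conclusion) compares programme children with two groups that did not receive the programme: HIV-infected children and HEU children.

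**The concern.** Confounding is absent from a group contrast only if the factors that drive the outcome are distributed alike in the groups. Randomisation would give that in expectation, but this study is not randomised. The Limitations sentence offers common exposure in its place, and that is a weaker property. Two groups can both be exposed to poverty, maternal illness and parental stress, yet to different degrees.

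Other parts of the protocol do not fill the gap. The Introduction accepts that deficits seen in HEU children may come from poverty, interrupted schooling and reduced wellbeing that accompany parental HIV, so these factors are recognised as acting on the outcome. Study procedures promises baseline comparability only among the HIV-infected infants, which leaves comparability with HEU children resting on the Limitations sentence.

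Two contrasts are affected. In HIV-infected versus HEU at 12 months, maternal or social differences may be read as an effect of infant HIV. In programme versus HEU, which belongs to the primary aim, the same differences would distort how near programme children appear to come to HEU children.

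**Working it through.** **Passages set side by side**

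| Element | Where | Does it give an adjusted group difference in scores? |
|---|---|---|
| 12-month means and counts, HIV-infected v HEU | Data analysis | No covariates named |
| t tests of characteristics between groups | Data analysis | No; may show imbalance, but no consequence is stated |
| Chi-squared and Kruskal-Wallis, three groups | Data analysis | No; neither test adjusts for covariates |
| Multiple (logistic) regression | Data analysis | No; dichotomised outcome, study group not named as a term |
| Baseline comparability | Study procedures | HIV-infected infants only |

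**The plan's own figure (Sample size).** Inputs: 45 per group, difference 25, SD 17 (cognitive), 16 (language), 20 (motor), two-sided 5% level.

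- SE = SD × √(2/45), which gives 3.58, 3.37 and 4.22.
- Power ≈ Φ(25/SE − 1.96). For the cognitive scale, 25/3.58 ≈ 6.98, so power = Φ(5.02).
- Power exceeds 99.9% on all three scales, which agrees with the stated figure of over 90%.

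Power is therefore not the problem. The issue is bias, which sample size does not remove.

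**Illustration of bias (assumptions).** The documents give neither the prevalence of any confounder by group nor its effect on scores. Suppose infant HIV has no true effect and confounding shifts the mean difference by b points. Then

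P(reject) = Φ(b/SE − 1.96) + Φ(−b/SE − 1.96).

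For SD 17:

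- b = 2: b/SE = 0.56, so P = Φ(−1.40) + Φ(−2.52) ≈ 8.6%.
- b = 3: b/SE = 0.84, so P = Φ(−1.12) + Φ(−2.80) ≈ 13.3%.

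For SD 16 the two values are 9.1% and 14.4%. For SD 20 they are 7.6% and 11.0%.

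**Range.** For a binary confounder, b = prevalence difference × effect on the score. A prevalence difference of 10 to 40 percentage points and an effect of 5 to 15 points give b from 0.10 × 5 = 0.5 to 0.40 × 15 = 6. With SD 17, rejection then runs from about 5% to 39%.

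The group size is itself an assumption here. Sample size fixes enrolment of 45 only for the intervention group. The size of the existing cohort is not stated, and its members are assessed at 12, 24 or 36 months, so the numbers of HIV-infected and HEU children assessed at 12 months are unknown.

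**The case against.** The strongest reply has four parts.

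1. *Adjustment is planned.* The multiple regression uses the very variables at issue, its HIV-related variables could include infection status, and between-group t tests would expose imbalance. This stands in part: it would be wrong to say the maternal and social data go unused. But the regression is framed as a search for risk factors for a poor outcome. It does not name study group and gives no adjusted difference in composite scores.

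2. *An article condenses.* Model terms may sit in a fuller document. That is fair for the covariate list. It does not cover an affirmative reassurance that the design cannot support.

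3. *The sentence may mean only the same kinds of environmental factor.* On that reading it is unobjectionable, but it also gives no protection against confounding, so it still needs qualifying.

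4. *The assumed bias is small.* A shift of 2 to 3 points is 8% to 12% of the planned 25-point difference. That is correct, and it limits the point: a difference of 25 would not be explained away by a shift of this size. Smaller observed differences could be.

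A reader might also infer more than the documents support. One stronger reading is that mothers who transmitted HIV had more advanced or less treated disease, so that the groups must differ. The documents contain no such data. The remark that "Maternal HIV infection can impact parenting skills which in turn influences" child outcomes does not help, because mothers in both groups have HIV. A second is that the protocol intends to read the difference as causal, or gives the Limitations sentence as its reason for not adjusting. It says neither. A third is that unstimulated HIV-infected versus HEU is a primary-aim comparison. It is not; the HEU contrast in that aim is with programme children.

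**Conclusion.** The point holds in limited form. The reassurance in the Limitations section is unsupported in a non-randomised study. Data analysis does not commit to a covariate-adjusted difference in composite scores for either HEU contrast, although relevant maternal and socioeconomic data are collected. The planned regression and the t tests narrow this gap without closing it.

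Whether the groups differ in maternal disease or social circumstances, and by how much, cannot be derived from the documents. The rise in false positives from 5% to about 9% or 13% rests on an assumed shift of 2 or 3 points, 45 per group, SD 17 and no true effect of infant HIV. The conclusion does not depend on those figures. It should be acted on because the better analysis is cheap.

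**What to change.** 1. In Limitations, delete the sentence, or qualify it to say that both groups face similar kinds of confounder, whose distribution may differ and will be examined.

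2. In Data analysis, for the HEU contrasts at 12 months, report beside the unadjusted comparison a linear-regression difference in each composite score with its 95% CI. Include study group as a term and a short prespecified covariate set: maternal viral load, CD4 count and ART history, plus socioeconomic items such as employment, housing and smoking or alcohol use.

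3. Use the measurements closest to birth where available. Study measures gives no timing for the maternal laboratory data or the household survey, so these covariates should not be described as preceding infection.

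4. Keep birth weight and gestational age to a sensitivity model, since infection before birth may affect them.

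The cost is mainly analysis wording, because the variables are already on the collection list; the availability of values near birth needs checking. Statistically it costs a few degrees of freedom, and the interval will widen if maternal viral load overlaps little between groups. Adjustment also leaves any unmeasured confounding in place, which the Limitations section already concedes for the survey.

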## Abbreviations

ART: antiretroviral treatment
BSID-III: Bayley Scales of Infant and Toddler Development, Third Edition
ECD: early childhood development
FBC: full blood count
HEU: HIV exposed uninfected
HIV: human immunodeficiency virus
LMIC: low- and middle-income countries
PSI-SF: Parenting Stress Index-Short Form
RMMCH: Rahima Moosa Mother and Child Hospital
